#### Ethics

The preGallStep trial will be conducted in compliance with the present protocol and the Helsinki Declaration [31]. The preGallStep trial also complies with the requirements from the Regional Ethics Committee of the Capital Region (H-20041609, 4 March 2021) and the Danish data protection laws (“databeskyttelsesforordningen” and “databeskyttelsesloven”) (P-2020-1056, 13 November 2020). The protocol was registered on ClinicalTrials.gov prior to the inclusion of the first participant (NCT04801238, 16 March 2021). Any substantial deviation from the protocol will only be implemented after review and approval from relevant regulatory authorities.

#### Safety

Both treatment strategies in the preGallstep trial are well-established treatments for CBDS and have been tested in the clinic with several observational studies and randomised trials in both Europe and in other continents and both techniques are, therefore, considered safe [32].

#### Adverse events

Adverse events will be noted in the patient medical chart. The surgeon on call will take relevant reactions to the event. At 90 days of follow-up, the coordinating investigator will assess if any serious adverse events (SAE), serious adverse reactions (SARs) or suspected unexpected serious adverse reactions (SUSARs) have occurred in order to report these to the regional ethics committee within 7 days of receiving the information.

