#### Central data monitoring

Central data monitoring will be initiated after the inclusion of one third of the participants and carried out every third month by a central data monitoring group consisting of investigators, including experienced clinicians, statisticians and trialists. The aim of the central data monitoring is to optimise completeness and quality and minimise deviations through blinded evaluation of the data [30].

Before the initiation of central data monitoring, we will publish a detailed central data monitoring plan including a description of the process.

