#### Data analysis

Statistical analysis will be conducted according to the intention-to-treat principle, and analyses will be adjusted for the stratifying variable “site” only. Since all participants included in the trial have CBDS according to the inclusion criteria and according to the best diagnostic modalities used in the clinic today (see above), the intention-to-treat principle can be used without any post-randomisation exclusions. Thereby, all patients with spontaneously passed stones at intra-operative cholangiography, lost to follow-up at 90 days or patients not undergoing the full two-step procedures will be included in the statistical analyses.

Feasibility outcomes will be assessed using descriptive statistics with the use of different types such as measures of variability and distribution.

Our secondary pilot outcome will be blindly assessed and analysed using logistic regression.

All continuous exploratory clinical outcomes will be analysed by linear regression, and other dichotomous exploratory clinical outcomes will also be analysed using logistic regression. Analyses will be performed in Stata (StataCorp LLC, Texas, USA), SAS (SAS Institute, North Carolina, USA) and/or R (R Core Team, Vienna, Austria).

Before the randomisation of the last participant, we will develop and publish a detailed statistical analysis plan with a detailed description of the analyses.

Due to the relatively small sample size, we will not conduct interim analyses. Thus, we will not employ a data monitoring committee.

All results will be presented with 95% confidence intervals (CI).

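### The only stated trial-level assessment of serious adverse events is at the 90-day follow-up, and the seven-day ethics report is tied to it, so reporting could run to about day 97

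*Protocol article*

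**What the plan says.** The Adverse events section of the protocol article sets out a short sequence.

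- When an event occurs: "Adverse events will be noted in the patient medical chart". The clinical response is local: "The surgeon on call will take relevant reactions to the event".
- At trial level: "At 90 days of follow-up, the coordinating investigator will assess if any serious adverse events (SAE", together with serious adverse reactions and suspected unexpected serious adverse reactions.
- The purpose and deadline of that assessment follow in the same sentence: "in order to report these to the regional ethics committee within 7 days of receiving the information".

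Two other sections bear on oversight. Under Data analysis: "we will not conduct interim analyses. Thus, we will not employ a data monitoring committee". Under Central data monitoring: "Central data monitoring will be initiated after the inclusion of one third of the participants". That monitoring then recurs every third month, is done by a group of investigators on blinded data, and aims at completeness, quality and fewer deviations. The Discussion adds that it is meant to show differences between sites, including in how the interventions and follow-up are carried out.

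**The concern.** The sentence combines a short deadline with a late trigger. A seven-day duty suggests prompt reporting, but the only assessment it is attached to comes at the end of each participant's follow-up. Deaths and unexpected serious reactions are placed in the same single step as all other serious events.

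What is at stake is how quickly a pattern could be recognised and reported while recruitment continues. The article itself gives reasons why an early pattern at one site is conceivable: the Background describes a high risk of pancreatitis after the endoscopic procedure and a need for special training and equipment for the one-step operation, the Trial sites section has sites joining in sequence, and the Discussion expects differences between sites in carrying out the interventions. The trial is also meant to shape a larger one, so a reporting rule left as it stands may be carried forward.

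**Working it through.** There is no figure in the plan to reproduce on this point. The sample size of 150 is stated to be pragmatic, and the information size from the trial sequential analysis plays no part here.

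**Inputs**
- Assessment at day 90, and report within 7 days of receiving the information (Adverse events).
- 150 participants over about 18 months (Sample size).
- Central monitoring from one third of inclusions (Central data monitoring).
- Assumptions: the coordinating investigator first learns of the event at the day-90 assessment; the full seven days are used; accrual is uniform; a month is 30.44 days. Day 0 is the start of the 90-day follow-up. The article counts this from randomisation in the Abstract and from the first surgical intervention in the Blinding section.

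**Step 1: longest delay on the stated sequence**
- Latest report: 90 + 7 = day 97.
- Delay for an event on day d: 97 − d days. For d = 1 this is 96 days; for d = 30, 67 days; for d = 60, 37 days.

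**Step 2: participants randomised meanwhile**
- Accrual rate: 150 / 18 = 8.33 per month.
- Over 90 days: 8.33 × 90 / 30.44 = 24.6, and 24.6 / 150 = 16%.
- Over 97 days: 8.33 × 97 / 30.44 = 26.6, and 26.6 / 150 = 18%.
- For an event on day 30: 8.33 × 67 / 30.44 = 18.3. For day 60: 8.33 × 37 / 30.44 = 10.1.

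**Step 3: does another stated step come earlier?**
- Central data monitoring starts after 150 / 3 = 50 inclusions. At the same rate that is 50 / 8.33 = 6.0 months into recruitment, so it does not cover the early period. Afterwards it recurs every three months, on blinded data, with a remit of data quality and differences between sites.
- The adjudication committee in the Blinding section reads charts up to 90 days after the first surgical intervention, to assess outcomes.
- The Safety section explains why both procedures are considered safe. It gives no reporting route.

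None of these is a trial-level safety step before day 90.

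**Step 4: how much depends on the trigger**
The deadline runs from receipt of the information. If a site told the coordinating investigator on day 3, the words would allow a deadline of 3 + 7 = day 10. With the day-90 assessment as first receipt, the deadline is day 97. The text gives only the second route and does not forbid the first.

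**The case against.** The strongest reply is that the passage is ambiguous rather than wrong. It does not say that serious events are looked at solely on day 90, and a clock that runs from receipt of information would start earlier if a site called earlier. This is a condensed article. Notification forms and expedited routes commonly sit in the full protocol, and the Ethics section states that the trial meets the ethics committee's requirements. All of this stands, and it limits the point to the timing that the article does state. It does not remove the point, because the sentence links the report to the day-90 assessment by purpose. If the full protocol has a prompt route, the article describes it misleadingly; if it has none, the procedure is slow.

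Three stronger readings are tempting, and the document does not support them.

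- A reader might infer that a death is bound to go unreported for three months. That is the outer limit of the stated sequence, not a certainty.
- A reader might infer that nobody in the trial could notice a cluster. Site staff chart and act on events at once, and central monitoring does look at differences between sites. What can be said is that no earlier trial-level safety route is stated.
- A reader might treat the missing data monitoring committee as the error. The article gives a reason, a small trial without interim analyses, and it describes both procedures as well established. Prompt reporting by sites does not depend on having such a committee.

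The accrual figures are also a worst case. Sites open in sequence, so early recruitment may be slower than the average. The 25 to 27 are people randomised in the interval, not people shown to be harmed.

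**Conclusion.** The point holds in this limited form. The article commits to one trial-level assessment of serious events, at 90 days, and attaches the ethics report to it. Followed as written, reporting of an event near the start of follow-up could take until about day 97, with a shorter delay for later events. About 25 to 27 further participants, 16 to 18% of the planned 150, could be randomised in the meantime. These figures rest on no earlier notice from the site, full use of the seven days and uniform accrual over 18 months. An unseen full protocol may already hold an earlier route. Even then the section needs correcting, because it does not say when sites must notify or what starts the seven days. Patient protection is involved and the correction is cheap, so it should be made.

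**What to change.** Amend the Adverse events section to state four things:

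1. The site notifies the coordinating investigator of each serious event when the site becomes aware of it.
2. The seven days for the report to the ethics committee run from that awareness.
3. The 90-day review is a completeness check on events already notified.
4. The coordinating investigator keeps a cumulative list of serious events by site, from the first participant.

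Counting from site awareness is a proposal of this review; the article cites no source for the start of the clock. If the full protocol already has such a route, bringing the article's wording into line with it is enough.

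The cost is a small extra reporting effort at sites, by form or e-mail. The article describes the web system only for enrolment and randomisation, so it should not be assumed that it can carry these notices. Under the Ethics section, a substantial change would need approval before use. Design, sample size and analysis are unaffected.

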## Discussion

The preGallstep trial is the first randomised clinical trial with blinded outcome assessment comparing two different approaches to CBDS. Our focus is not just to compare the two different approaches to CBDS, but also to focus on patient-reported outcomes.

This randomised feasibility and pilot clinical trial have a pragmatically chosen sample size, with associated risks of random errors in the assessment of complication estimates. Yet, we have based our estimates for this feasibility and pilot trial on previous trials and on the flow of relevant patients through the surgical departments in Denmark.

The variations in the inclusion procedures of each trial site due to patients being both acute and ambulant could cause one of the bigger challenges in estimating feasibility issues and implementing changes in procedure in a larger pragmatic trial. We will implement a central data monitoring scheme designed to illustrate “inter-site” differences and the causes of these [30]. These differences are both regarding screening and randomisation, but also executing the trial interventions and follow-up. This monitoring plan will be published separately to ensure complete transparency.

We have not established a priori threshold to judge whether to proceed with a future definitive trial. There are many external factors that influence the conduction of a multicentre RCT such as regional politics and changes in clinical treatment guidelines. Therefore, our focus is not to pragmatically define a threshold but to evaluate these regional differences in planning a future trial. Also, there may be differences in handling complications to surgery at trial sites. Consequently, differences in the Clavien-Dindo score assessments among sites are expected. This may affect the generalisability of this feasibility trial.

The data collected in the present trial will not be pooled with data for a subsequent larger pragmatic trial since there will be differences in procedures. However, the data from the present trial will be available for later systematic reviews with meta-analysis.

The Danish guidelines for the treatment of gallstone disease were published in 2006 [33], and an interdisciplinary group of clinicians has been working on a revision since 2021. In the revised guidelines [34], a one-step procedure is recommended for the treatment of CBDS. This is also recommended in the ESGE guidelines from 2019 [3]. Both guidelines recommend one-step procedures without discriminating between laparoscopic common bile duct exploration or rendez-vous endoscopic retrograde cholangiography during laparoscopic cholecystectomy. The recommendations for rendez-vous is, however, weak with each trial underpowered [34]. As shown in the present study, this also holds for an updated meta-analysis of the question. In the ESGE guidelines, it is emphasised that implementing rendez-vous ERC does carry logistical problems related to the prolonged surgical times and the need to perform ERC in an environment that is not adapted for endoscopy.

In this protocol, we have provided the background and rationale for conducting a trial that compares one-step versus two-step procedures for the removal of CBDS. We have shown an insufficient sample size of previously conducted randomised trials according to TSA. Although there is a tendency to recommend a one-step procedure by some, it is still important to explore the feasibility of implementing such treatments in the clinical setting as a try to obtain better evidence for the recommendations in our clinical guidelines.

## Data Availability

After the results have been published, we aim to make a depersonalised dataset publicly available on, e.g. ClinicalTrials.gov and/or the ZENODO database. The final choice will reflect which platform(s) that are compliant with current legislation at that time.
